### Statistical methods

#### Sample size and justification

*Estimation of key trial parameters*

The primary objective of this pilot trial is to demonstrate the feasibility of running a definitive, multi-centre trial of the MiQuit interevention within an NHS context; with 400 participants, the following key parameters will be estimable within the precision indicated (figures presented are margin of error = half width of 95% confidence interval):the recruitment rate of participants from within smokers attending trial centres/hospital to within +/− 1%,for individual trial groups, proportion of participants with validated smoking cessation between 4 weeks after randomisation until late pregnancy to within +/− 4%, andfor both trial groups, the combined proportion of participants who quit in late pregnancy (cessation as defined above) to within +/− 3%, assuming that the actual proportion of participants quitting is around 10%.2.*Estimate for short-term efficacy*

A secondary objective of this pilot trial is to estimate the effectiveness of the MiQuit intervention for promoting smoking cessation. Providing evidence to support the notion that this intervention is likely to be effective would increase the research team’s future chances of obtaining funding to conduct a definitive trial. We will investigate efficacy of MiQuit at 4 weeks after randomisation by comparing self-reported, 7-day, point-prevalence, cessation rates between trial groups. It should be noted that this is a surrogate end point for that which we plan to use in any definitive trial; a potential strength of using this is that event rates (that is, proportion of participants achieving cessation) are likely to be higher at this time point, which is closer to randomisation than the late pregnancy-assessment point, and this could provide greater power to detect between group differences. A potential disadvantage is that the relationship between this surrogate endpoint and cessation in late pregnancy (approx 36 weeks) is not known; consequently, findings using data obtained at this time point should not be used in isolation to assess whether or not a definitive trial should be conducted. Consequently, using 95% and 80% confidence intervals (CIs), Tables 2 and 3 illustrate for this trial with 400 participants, the precision for detecting different ORs representing differences between groups over a range of control group event (that is, quit) rates. The choices of parameters for the tables are explained below.

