**Methods/Design:**

This will be a multi-centre, parallel group RCT. Participants are being identified in 16 English antenatal care settings and must be >16 years old, pregnant, <25 weeks gestation, smoke >1 daily cigarette, have smoked >5 daily cigarettes before pregnancy, and able to understand texts in English. After consenting and the collection of baseline data, participants are randomised to control or intervention groups in a 1:1 ratio; randomisation is stratified by trial site and gestation and employs computer-generated pseudo-random code using random permuted blocks of randomly varying size, and held on a secure server. All participants receive a National Health Service (NHS) leaflet aimed at helping them to stop smoking. Intervention group women also receive the 12-week MiQuit programme of tailored, supportive, interactive text message, self-help cessation support. Women are followed up by telephone 4 weeks after randomisation and at 36 weeks gestation. The study aims to recruit 400 women, and with this sample we will be able to estimate trial centres’ recruitment rates to within +/−1% (margin of error = half width of 95% confidence interval); individual trial groups’ ascertainment of rates for smoking outcomes between 4 weeks after randomisation until approximately 36 weeks gestation to within +/−4%, and across both groups, the combined cessation rate at 36 weeks +/−3%.

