Before MiQuit could be used in routine care, a definitive randomised controlled trial would need to prove its effectiveness, so obtaining further evidence concerning its efficacy is appropriate. However, such a trial would need to be very large and expensive and, currently, there is insufficient information to justify conducting this. For example, it is not known if cessation encouraged by MiQuit, in the pilot trial, which was measured, at 12 weeks after randomisation (around mid-pregnancy), persists beyond this point. However, sustained cessation throughout pregnancy would be required before one could expect this potentially-useful intervention to have a meaningful impact on fetal health. Also, there is only very limited information with which one could plan a definitive trial such that this made efficient use of research resources; for example, likely recruitment and follow-up rates need determining. Consequently, we propose a pilot trial, which will investigate whether or not it is possible to evaluate MiQuit in a multi-centre RCT located within the NHS research infrastructure, taking full advantage of appropriate NHS research network resources. This study will provide estimates for the following parameters, which will be of crucial importance when deciding upon resources required for a definitive trial: the range of likely recruitment rates in different centres; quit rates amongst trial participants; feasibility of assessing smoking status of trial participants in later pregnancy; ascertainment rates obtained; and the likely effect of MiQuit when women are offered this in NHS settings. Findings from the pilot trial will permit estimation of the likely impact of MiQuit being introduced into routine clinical practice.

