### Data analysis

Members of the research team, led by the study statistician, will undertake the analyses. A full statistical analysis plan will be finalised and agreed by the Trial Steering Committee prior to data analysis. Initially, participants in the two intervention groups will be described separately with respect to the following:CentreAge at randomisationEthnic group (white, other)Gestation at randomisation (<16 weeks, 16+ weeks)Heaviness of smokingNumber of births beyond 24 weeks,Previous history of prenatal smokingPartner/significant other’s smoking statusParticipant’s health status (EQ5D) Participant’s motivation to quit

Analyses will primarily address the feasibility objectives of the study. We will determine the recruitment rate, with 95% confidence intervals, of participants who take part in the study from pregnant smokers attending trial centre. For each trial treatment group, we will estimate the proportions of participants, with 95% confidence intervals, achieving validated smoking cessation between 4 weeks after randomisation until late pregnancy (at approximately 36 weeks gestation). We will also estimate the proportion of participants, with 95% confidence intervals, who achieve validated smoking cessation in late pregnancy (approximately at 36 weeks gestation) for both trial groups combined.

We will perform chi-squared tests to assess the association for the proportion of participants who achieve 4-week and late-pregnancy smoking outcomes between the trial treatment groups. Logistic regression models will then be used to compare the outcomes between the two trial groups with adjustment for factors used to stratify the randomisation (centre and gestation at randomisation; <16 weeks versus ≥16 weeks) through including these as fixed covariates in the model. These analyses will be pragmatic and based on intention-to-treat. Additionally, we will create the following graphs to look at the pattern of the outcome response across centres:Average outcome in the intervention group versus the average outcome in the control group per centre.Average difference in outcome between the intervention and control groups per centre versus centre.

Further multiple logistic regression analyses will be conducted to assess the strength of association between baseline covariates and 4-week and late-pregnancy smoking outcomes, which will include the following:Heaviness of smoking.Partner/significant other’s smoking status.Education as a measure of SES.

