Third, recruitment rates from this study will be vital for assessing the feasibility of delivering a large definitive RCT investigating smoking cessation in pregnancy and using English National Health Service (NHS) research structures. Since 2006, the English NHS has developed and revised research networks, funded from the health service budget and orientated towards delivering clinical research; there is a particular focus on RCTs that influence clinical practice [24]. Networks provide staff working across the NHS whose remit is to recruit to research studies and researchers who successfully access network staff support can efficiently deliver multi-centre RCTs. However, negotiating access to research networks and subsequently finding the most efficient ways of combining their efforts with those of a university-based research team can be challenging and, significantly the two most recent English pregnancy smoking cessation trials [18,19] were completed with relatively little research network input. To date, overall pilot trial recruitment has been strong and it appears that study methods could, feasibly be used to recruit to a larger definitive study. However, across the 16 trial centres from which this pilot recruits, there has been marked variation in recruitment rates. Consequently, lessons learned from our planned pilot trial process evaluation should help us to better understand the reasons for different recruitment rates in different centres and, potentially to enhance the research network staff experience of recruiting to the trial for any future study.

Given the nature of this pilot trial, discussion has principally focussed on methodological issues. However, if after this study, a definitive RCT is conducted and MiQuit is found to be effective for smoking cessation in pregnancy, this very cheap and likely (in that circumstance) highly cost-effective intervention could easily be made very widely available in many different ways to support smoking cessation in pregnancy.

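### The ±1% margin for recruitment rates holds only as a pooled binomial figure: it is not reached in individual centres and makes no allowance for variation between them

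*Protocol article*

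**What the plan says.** Recruitment is the first parameter listed under Primary objective, under Feasibility outcomes and under Sample size and justification. The last of these says that "with 400 participants, the following key parameters will be estimable within the precision indicated", defines the figures as half-widths of 95% confidence intervals ("figures presented are margin of error = half width of 95% confidence interval"), and promises "the recruitment rate of participants from within smokers attending trial centres/hospital to within" ±1%. That wording reads most naturally as one pooled rate.

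The abstract (Methods/Design) puts it at centre level: "we will be able to estimate trial centres’ recruitment rates to within" ±1%. The Background names "the range of likely recruitment rates in different centres" among the parameters of crucial importance for resourcing a definitive trial.

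Data analysis plans a single quantity: "We will determine the recruitment rate, with 95% confidence intervals, of participants who take part in the study from pregnant smokers attending trial centre". It does not name the interval method. The Discussion reports that "across the 16 trial centres from which this pilot recruits, there has been marked variation in recruitment rates". The Recruitment section adds that centres use one or both of two recruitment methods, according to local resources.

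**The concern.** One figure, ±1%, is offered for two different quantities: the overall rate and the rates of the centres. A sample of 400 spread over 16 centres cannot give both the same precision. The figure also comes without the recruitment rate or the number of smokers that produced it. The 10% in the same list is an assumed quit rate, not a recruitment rate.

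The second issue is the use to be made of the estimate. The definitive trial could need over 3,000 women (Discussion), so it may well have to recruit beyond these 16 centres. A margin that treats all smokers as one homogeneous sample then leaves out the spread between centres. At stake is how confidently the number of sites and the length of recruitment for that trial can be predicted.

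**Working it through.** **Inputs from the article.** 400 recruits and 95% half-widths (Sample size and justification); 16 centres (abstract and Discussion). **Not given, so assumed:** the recruitment rate r, an equal split of recruits over centres, and the between-centre SD.

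**1. The companion figures reproduce.** With the article's 10% quit rate:
- one arm: 1.96 × √(0.1 × 0.9/200) = 4.2%, stated as 4%;
- both arms: 1.96 × √(0.1 × 0.9/400) = 2.9%, stated as 3%.

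So the article uses a simple binomial half-width rounded to a whole percent.

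**2. The pooled recruitment rate.** With k recruits at rate r, the number of smokers is N = k/r, and the half-width is 1.96 × √(r(1 − r)/N) = 1.96 × r × √((1 − r)/k). Because r is not stated, ±1% cannot be reproduced outright, only matched to a range of rates. For a single centre, k = 400/16 = 25.

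| r | Smokers, all centres | Pooled, k = 400 | Average centre, k = 25 |
|---|---|---|---|
| 5% | 8,000 | ±0.48 | ±1.9 |
| 10% | 4,000 | ±0.93 | ±3.7 |
| 10.8% | about 3,700 | ±1.00 | ±4.0 |
| 15% | about 2,670 | ±1.36 | ±5.4 |
| 20% | 2,000 | ±1.75 | ±7.0 |

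(Half-widths in percentage points.) The pooled margin is exactly 1% at r of about 10.8%. With whole-percent rounding it fits r from about 5.2% to 16.8%.

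**3. Can ±1% describe both levels?** An average centre reaches ±1% only if r is about 2.6% or less (1.96 × 0.026 × √(0.974/25) = 1.0%), or about 3.9% or less if 1.5% is allowed to round down. At those rates the pooled margin would be about 0.25% to 0.4%. No single rate makes ±1% right for both, and centres with fewer than 25 recruits do worse than the average.

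**4. Allowing for centre when looking beyond these 16.** Take r = 10%, so 4,000/16 = 250 smokers per centre. The half-width for the mean centre rate is t × √((SD² + 0.1 × 0.9/250)/16), with t = 2.131 on 15 df. The SD is an assumption:

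| Assumed between-centre SD | Half-width |
|---|---|
| 0 | ±1.01 (±0.93 with 1.96) |
| 1 point | ±1.14 |
| 2 points | ±1.47 |
| 3 points | ±1.89 |
| 5 points | ±2.85 |

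**5. A new centre, same assumptions.** The symmetric form, t × SD × √(1 + 1/16), gives ±6.6 points for an SD of 3 and ±11.0 for an SD of 5. The second runs below zero around 10%, so the logit scale is needed. There the SD is about SD/(0.1 × 0.9), that is 0.333 and 0.556. The limits are logit(0.10) ± 2.131 × 0.333 × 1.031 = −2.197 ± 0.732, or about 5% to 19%; and −2.197 ± 1.221, or about 3% to 27%.

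**The case against.** The strongest reply is that the main text promises a pooled rate among smokers attending the trial centres. For the aggregate rate in these 16 centres, between-centre variance does not widen the interval, and a binomial margin is adequate. That stands. The widening in step 4 answers a different question, about centres in general, and a mean of centre rates is not the same estimand as the pooled rate.

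A reader might also infer that the planned confidence interval is itself too narrow, or that the analysis treats women as independent. The document does not support this. Data analysis names no interval method and defers to a full statistical analysis plan that is not at hand.

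Nor does ±1% require a rate of 10.8% or lower. The article rounds to whole percents, so a rate of 15% (±1.36) would also be printed as 1%.

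The size of the widening is conditional. No between-centre SD is given, and the variation reported in the Discussion may refer to numbers recruited rather than the proportion of smokers enrolled. It was also seen during recruitment, so it was not available when the precision was first set. Differences between centres are not overlooked either: the article will examine both recruitment methods, collect reasons for non-recruitment and interview site staff. Finally, no progression rule depends on the ±1%.

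None of this rescues the abstract's centre-level wording, which fails on 400 recruits and 16 centres alone. The qualitative work does not supply a between-centre variance.

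**Conclusion.** The point holds for the stated margin. As a claim about the centres' rates, ±1% is wrong at every recruitment rate for which it describes the pooled margin. At a 10% rate an average centre has ±3.7 points, about four times the pooled ±0.93; the factor is √16 under an equal split.

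As a pooled figure, ±1% is plausible for rates of about 5% to 17%, but its basis is not stated. It is sufficient for these 16 centres taken together and too optimistic when carried over to other centres. How much too optimistic cannot be settled from the document: at 10%, an SD of 1 point hardly matters (±1.14), while 3 to 5 points gives ±1.89 to ±2.85. Those figures are illustrations, not estimates for this trial, and no fault in the planned analysis has been shown.

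**What to change.** - **Wording, in the abstract and in Sample size and justification:** state the assumed recruitment rate and the number of smokers behind ±1%, say that it is a pooled figure that excludes variation between centres, and drop it for individual centres.
- **Analysis, in the statistical analysis plan:** keep the pooled rate. Report each centre's rate with its own confidence interval. Beside the pooled rate, give an estimate that allows for between-centre variation, for example from a random-intercept logistic model, with a 95% prediction interval for a new centre computed on the logit scale so that it stays above zero.

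**Cost:** the recruitment counts and smoker denominators needed for the planned rate, kept by centre, are enough. The work is a text correction and a short extra analysis. The stated precision becomes less favourable, and with only 16 centres the between-centre variance will itself be estimated imprecisely.

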**Table 2 Tab2:** **Estimates for treatment effect: precision estimates presented as 95% confidence intervals**

***95% CI Odds ratio***	**10% control event rate N = 200 in each group**	**15% control event rate N = 200 in each group**	**20% control event rate N = 200 in each group**
1.3	0.70 to 2.42	0.77 to 2.20	0.81 to 2.09
1.5	0.82 to 2.76	0.90 to 2.51	0.94 to 2.39
1.8	1.0 to 3.26	1.09 to 2.98	1.14 to 2.85

**Table 3 Tab3:** **Estimates for treatment effect: precision estimates presented as 80% confidence intervals**

***80% CI Odds ratio***	**10% control event rate N = 200 in each group**	**15% control event rate N = 200 in each group**	**20% control event rate N = 200 in each group**
1.3	0.87 to 1.95	0.92 to 1.83	0.95 to 1.77
1.5	1.01 to 2.23	1.07 to 2.10	1.11 to 2.03
1.8	1.22 to 2.65	1.29 to 2.51	1.33 to 2.43

*Control group event (quit) rates*: There are few data with which we can estimate control group event (that is, proportion of participants achieving cessation) rates at 1 month after randomisation, but accurate estimates are important to inform meaningful sample size estimates. One recent trial (MiQuit feasibility trial), tested a very similar version of this trial’s intervention, but in this study 7-day point-prevalence abstinence was measured in similar manner as we propose at *12 weeks* after randomisation, rather than at 1 month after; in this trial, the control group quit rate was 19.6% [11]. Two recent UK trials have enrolled pregnant smokers, albeit with different characteristics, and have measured cessation outcomes at 1 month after randomisation. A trial of nicotine patches found a 14% control group rate of self-reported, *prolonged* cessation between randomisation and 1 month [18], and control group women recruited to an exercise intervention RCT had a 13.7% validated abstinence rate, again for reported, *prolonged* abstinence during the same period (unpublished findings) [19]. Overall, therefore, assuming that control group quit rates will fall within in a 10 to 20% range seems reasonable.3.*Estimates for treatment effect*

MiQuit is a self-help intervention and a systematic review of self-help interventions used for smoking cessation in pregnancy found a pooled estimate for the effectiveness of these, which corresponds to an Odds Ratio (OR) and (95% CI) in favour of using such interventions of 1.83 (1.23 to 2.73) [7]. Using data obtained at 3 months after randomisation, the MiQuit feasibility trial found an OR in favour of using MiQuit of 1.68 (0.66 to 4.31) [11]. Consequently, using a range of OR from 1.3 to 1.8 is appropriate.

*Estimating cessation in late pregnancy:* For modelling analyses, we will use a trial-derived estimate for the treatment effect of the intervention derived from between-group differences in validated, longer term quit rates, measured in late pregnancy (that is, at approximately 36 weeks gestation). Again deriving this estimate is a secondary objective of the trial. Tables 4 and 5 use 95% and 80% confidence intervals (CIs), to illustrate for this trial with 400 participants, the precision for detecting different ORs representing differences between groups over a range of control group event (that is, proportion of participants achieving cessation) rates. The proportion of participants in the control group who quit is based on 5% and 10%, as this reflects findings in the three trials described above [11,18,19].

**Table 4 Tab4:** **Estimating cessation in late pregnancy: precision estimates presented as 95% confidence intervals**

***95% CI Odds ratio***	**5% control event rate N = 200 in each group**	**8% control event rate N = 200 in each group**	**10% control event rate N = 200 in each group**
1.3	0.56 to 3.05	0.65 to 2.58	0.70 to 2.42
1.5	0.66 to 3.44	0.77 to 2.93	0.82 to 2.76
1.8	0.81 to 4.02	0.94 to 3.46	1.0 to 3.26

**Table 5 Tab5:** **Estimating cessation in late pregnancy: precision estimates presented as 80% confidence intervals**

***80% CI Odds ratio***	**5% control event rate N = 200 in each group**	**8% control event rate N = 200 in each group**	**10% control event rate N = 200 in each group**
1.3	0.75 to 2.27	0.83 to 2.04	0.87 to 1.95
1.5	0.87 to 2.58	0.97 to 2.33	1.01 to 2.23
1.8	1.06 to 3.05	1.18 to 2.76	1.22 to 2.65

### Data analysis

Members of the research team, led by the study statistician, will undertake the analyses. A full statistical analysis plan will be finalised and agreed by the Trial Steering Committee prior to data analysis. Initially, participants in the two intervention groups will be described separately with respect to the following:CentreAge at randomisationEthnic group (white, other)Gestation at randomisation (<16 weeks, 16+ weeks)Heaviness of smokingNumber of births beyond 24 weeks,Previous history of prenatal smokingPartner/significant other’s smoking statusParticipant’s health status (EQ5D) Participant’s motivation to quit

Analyses will primarily address the feasibility objectives of the study. We will determine the recruitment rate, with 95% confidence intervals, of participants who take part in the study from pregnant smokers attending trial centre. For each trial treatment group, we will estimate the proportions of participants, with 95% confidence intervals, achieving validated smoking cessation between 4 weeks after randomisation until late pregnancy (at approximately 36 weeks gestation). We will also estimate the proportion of participants, with 95% confidence intervals, who achieve validated smoking cessation in late pregnancy (approximately at 36 weeks gestation) for both trial groups combined.

We will perform chi-squared tests to assess the association for the proportion of participants who achieve 4-week and late-pregnancy smoking outcomes between the trial treatment groups. Logistic regression models will then be used to compare the outcomes between the two trial groups with adjustment for factors used to stratify the randomisation (centre and gestation at randomisation; <16 weeks versus ≥16 weeks) through including these as fixed covariates in the model. These analyses will be pragmatic and based on intention-to-treat. Additionally, we will create the following graphs to look at the pattern of the outcome response across centres:Average outcome in the intervention group versus the average outcome in the control group per centre.Average difference in outcome between the intervention and control groups per centre versus centre.

Further multiple logistic regression analyses will be conducted to assess the strength of association between baseline covariates and 4-week and late-pregnancy smoking outcomes, which will include the following:Heaviness of smoking.Partner/significant other’s smoking status.Education as a measure of SES.

These variables have been chosen as potentially requiring adjustment because, in previous studies, they have been shown to be associated with smoking cessation in pregnancy [20,21].

Other smoking outcomes will be analysed using similar methods: 95% confidence intervals will be presented along with exact two-sided *P* values. Descriptive analyses will be performed to assess the effect of the intervention on the use of NHS cessation support, use of interactive features of the intervention and social cognitive variables.

We also plan to explore the mechanism of effect for the MiQuit intervention that is, how the intervention might change smoking behaviour. For this, we will undertake mediation analyses to explore whether potential changes in social cognitive determinants of smoking cessation explain changes in quitting behaviour. This will be a secondary analysis and, therefore, covered in a separate paper rather than in the main trial outcomes paper.

Health economic analysis will investigate the potential incremental cost-effectiveness of MiQuit using costs (actual and estimated) of delivering the intervention and estimates for its effectiveness derived from the trial. Models developed in previous studies will be used to project the likely cessation rates into longer term estimates of life years gained.

